**1. Trial protocol outline**

(1) Trial food: Food product containing royal jelly (trial project), food product without royal jelly (placebo)

(2) Objective: To evaluate the effects of 8 continuous weeks of consumption of a food product containing royal jelly on subjective assessment of dry eyes as well as ophthalmological examination results, and to compare these effects to those of a placebo.

(3) Subjects: Men and women aged 20 to 60 years with subjective symptoms of dry eyes

(4) Number of subjects at the start of consumption: 50 (trial product: 25 participants; placebo: 25 participants)

(5) Trial design: Randomized, double-blind, placebo-controlled, parallel-group trial

(6) Amount of functional ingredient consumed: Royal jelly 7,200 mg (raw product) per day

(7) Method of consumption: 2 capsules swallowed whole with water after meals, 3 times per day

(8) Period of consumption: 8 weeks

(9) Planned trial duration: May 2014 to March 2015

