**6. Number of subjects, allotment method**

6.1. Number of subjects

There will be 50 subjects when consumption is started—25 subjects taking the trial product and 25 subjects taking the placebo.

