**15. Evaluation methods**

15.1 Evaluating efficacy

(1) Primary outcomes: subjective dry eye symptoms, BUT, keratoconjunctival disorders, Schirmer’s test

(2) Secondary outcomes: functional vision

(3) Efficacy evaluation methods

For each item, values before consumption and at each time point after consumption will be compared between the trial group and the placebo group using a 2-sample t-test. The amount of change from before consumption to each time point after consumption will be compared between the trial group and the placebo group using a 2-sample t-test. Values at each time point after consumption will be compared to values before consumption in each group using a 1-sample t-test.

For the baseline characteristics of patients with dry eye, Student’s t-test (p ≥ 0.05 by the F-test) will be used for comparison of age, and Pearson chi-square test will be used for categorical data of gender and dry eye diagnosis. Repeated measures analysis of variance followed by Tukey's honest significant difference (HSD) post hoc test will be used for analysis of dry eye symptoms. For the biochemical analysis, paired t-tests will be used for within-group comparisons and the F-test, followed by Student’s t-test (p≥0.05 by the F-test) will be used for between-group comparisons (placebo vs. RJ). A p-value of <0.05 was considered statistically significant. 16.2. Evaluating safety

(1) Outcomes

These are adverse events confirmed from interviews and journal entries (subjective symptoms), and abnormal variations in body weight and scientific examination values. For examination values, changes in items will be checked: body weight, systolic blood pressure, diastolic blood pressure, heart rate, and biochemical data.

(2) Evaluation methods

The number of adverse events and abnormal variations will be totaled to create a table. If the same adverse event occurs in the same subject multiple times, it will be treated as one event. To evaluate changes in examination values, measurements before consumption and at each time point after consumption will be compared using a 1-sample t-test. Figures will be displayed as mean ± standard deviation (or standard error). The significance level will be 2-sided 5%.

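### The primary symptom outcome has two unranked analyses in Section 15.1(3), and the repeated-measures ANOVA with Tukey HSD does not isolate the between-arm difference after 8 weeks

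*Protocol*

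**What the plan says.** Protocol Section 15.1(1) lists "Primary outcomes: subjective dry eye symptoms, BUT, keratoconjunctival disorders, Schirmer’s test". Section 15.1(3) then describes the tests in two paragraphs.

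- The first paragraph covers all outcomes: "For each item, values before consumption and at each time point after consumption will be compared between the trial group and the placebo group", by 2-sample t-test. It adds a second between-arm t-test: "The amount of change from before consumption to each time point after consumption will be compared between the trial group and the placebo group". Within-group 1-sample t-tests against the pre-consumption value follow.
- The second paragraph returns to symptoms alone: "Repeated measures analysis of variance followed by Tukey's honest significant difference (HSD) post hoc test will be used for analysis of dry eye symptoms".

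The efficacy text closes with "A p-value of <0.05 was considered statistically significant". The two-sided 5% level is stated under the safety evaluation. Neither symptom analysis is called primary, supportive or a replacement for the other. No primary time point is named. The ANOVA terms, the set of means that Tukey compares and the error term are not given. The objective in Section 1 is "To evaluate the effects of 8 continuous weeks of consumption of a food product containing royal jelly on subjective assessment of dry eyes" and to compare the effects with placebo.

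**The concern.** Symptoms are one of the items in the first paragraph and the sole subject of the ANOVA sentence in the second, so both instructions apply to the same primary outcome. They can give different answers. With no ranking, either can be presented as the planned result after unblinding, and the stated 5% then does not describe the chance of a false positive.

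The second analysis also answers a different question. A repeated-measures ANOVA on two arms and three visits offers a group main effect averaged over visits and an interaction spread over visits. Neither is the arm difference after 8 weeks, and all-pairwise Tukey comparisons do not single it out.

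**Working it through.** **Inputs from the protocol.** There are "25 subjects taking the trial product and 25 subjects taking the placebo" (Section 6.1). The symptom questionnaire is scheduled at pre-consumption, week 4 and week 8 (schedule table; it is also given at the preliminary visit). The level is two-sided 5%. The protocol gives no effect size, SD or power, so it has no figure of its own to reproduce here.

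**Assumptions.** Normal data, equal SD at each visit (set to 1), compound symmetry with within-subject correlation ρ of 0.3 to 0.8, and all 25 per arm analysed. The protocol gives no correlation. Each setting used 20,000 simulated trials.

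**Step 1: two live analyses, no true effect.** Percentage of trials significant at 5%:

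| ρ | t-test, change to week 8 | ANOVA interaction | Either of these | Either week 8 t-test (value or change) | Any of the two t-tests, group F or interaction F |
|---|---|---|---|---|---|
| 0.3 | 5.1 | 5.1 | 7.7 | 8.9 | 14.3 |
| 0.5 | 5.0 | 4.7 | 7.3 | 9.1 | 13.6 |
| 0.7 | 5.1 | 4.9 | 7.5 | 9.5 | 13.8 |
| 0.8 | 5.0 | 5.0 | 7.5 | 9.7 | 13.6 |

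Each test alone holds its level. The excess comes from having more than one and no rule for choosing.

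**Step 2: what the ANOVA tests.** Take a true week 8 difference of 0.81 SD (assumed; the t-test on week 8 values then has 80% power).

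- With no effect at week 4, the group main effect estimates (0 + 0 + 0.81)/3 = 0.27 SD. Its simulated power is 17–25%.
- With half the effect at week 4, it estimates (0 + 0.405 + 0.81)/3 = 0.405 SD. Its power is 32–48%.
- The interaction has (2 − 1)(3 − 1) = 2 df and tests any departure from parallel profiles. It can be powerful (56–99.8% across these settings), but a significant result does not say that the arms differ at week 8.

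**Step 3: Tukey, depending on the means compared.** The critical |t| is q/√2, with q the 95% point of the studentised range.

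- *Two means, 48 df:* q/√2 = 2.011, equal to t(48). Tukey and the t-test coincide.
- *Six arm-by-visit cells:* there are 6 × 5/2 = 15 pairs. Three compare arms at the same visit (one of them before consumption), six are within an arm, and six cross both arm and visit. The critical value is 2.908 at 96 df and 2.888 at 144 df.
- *Power, six cells, total variance:* by normal approximation, 1 − Φ(2.91 − 2.82) = 46%, where 2.82 = 1.98 + 0.84 is the shift giving 80% power. By noncentral t with shift 0.81 × √12.5 = 2.864 and 144 df, it is 49%. In these simulations the verdict differed from that of the t-test on change in 33–51% of trials.
- *Six cells, within-subject error term:* that term estimates σ²(1 − ρ), whereas the arm contrast at one visit has variance 2σ²/25. The SE is therefore too small by √(1 − ρ): 0.71 at ρ = 0.5 and 0.55 at ρ = 0.7. The error rate is 2[1 − Φ(2.91√(1 − ρ))] = 1.5%, 4.0% and 11.1% at ρ = 0.3, 0.5 and 0.7. Simulation gave 1.6%, 4.3% and 11.6%, and 19.9% at ρ = 0.8.

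**The case against.** One defence is that the specific sentence overrides the general one, leaving ANOVA/Tukey as the only symptom analysis. The text does not say so. If it were so, the symptom outcome would lose the only between-arm test of change to week 8 that the protocol writes down, and Step 2 would apply in full.

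A stronger objection is that the protocol already contains the right contrast: change from pre-consumption is compared between arms at each later time point, which includes week 8. That stands. What is missing is its precedence, not the test.

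A reader might also infer more than the protocol supports:

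- *That the plan uses a wrong critical value or error term.* It states neither, nor which means Tukey compares, and these are details that an analysis plan may settle. The misfit arises with six cells and vanishes with two means. Even with the within-subject error term, the six-cell test exceeds 5% per contrast only above a correlation of roughly 0.5 to 0.55.
- *That repeated-measures ANOVA would lose subjects with a missed visit.* Section 14.1 already limits the efficacy set to those who complete the whole schedule, so essentially nobody further is lost.
- *That week 8 is the declared primary time point.* It is inferred from the 8-week objective in Sections 1 and 2.
- *That a mixed model is required.* In a completer set it has little advantage over a t-test or ANCOVA.

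**Conclusion.** The contradiction is in the text and needs no assumption: one primary outcome, two prescribed analyses, no order between them. This is not a detail left to an analysis plan, because such a plan would have to overrule one of two protocol sentences. The size is moderate. The false-positive rate is about 7.5% rather than 5% when either the week 8 t-test on change or the ANOVA interaction may count, and about 14% if the t-test on week 8 values and the group main effect may count as well. These figures rest on the assumed compound symmetry and correlations, and barely move across the correlations tried.

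That ANOVA with Tukey does not isolate the 8-week arm difference follows from the structure of the tests, given the objective. The loss of power to about 46–49% and the understated SE are conditional on a six-cell Tukey family; the SE also depends on the error term chosen. They are reasons not to leave Tukey as the primary analysis, not established errors in it.

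**What to change.** In Section 15.1(3), state that the primary analysis of subjective dry eye symptoms is the single between-arm comparison of change from pre-consumption to week 8, reported with a 95% CI. The t-test already in the protocol will serve; with 48 df its simulated error rate was 5.0–5.1% at every correlation tried. ANCOVA with the pre-consumption value as covariate is preferable: under the same assumptions its residual variance is (1 − ρ²)σ² against 2(1 − ρ)σ² for change, a ratio of (1 + ρ)/2, or 0.65 to 0.85 for ρ of 0.3 to 0.7. Label repeated-measures ANOVA with Tukey HSD and the remaining symptom tests as supportive, or delete them. If Tukey stays as supportive, name the means it compares and the error term. A mixed model is optional.

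The cost is about two sentences and no new data. Section 16.3 also requires the sponsor's written consent and ethics re-approval for a protocol change. The change should be made before the allocation table is unsealed.

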**9. Protecting personal, and or other information**

The people involved in the trial will give full consideration to protecting a subject’s personal information and privacy when handling the consent forms and case report forms, and when publishing the data. Filling out case report forms, publishing articles, and submitting materials to regulatory authorities should be done in such a manner that a subject cannot be identified (for example assigning them identification numbers) to protect their privacy.

| Examination day | | Preliminary period |  | Consumption period (8 weeks) | | |
| --- | --- | --- | --- | --- | --- | --- |
|  | | Preliminary |  | Pre-consumption | Week 4 of consumption | Week 8 of consumption |
| Inclusion, allotment | |  | ○ |  |  |  |
| Lifestyle questionnaire | | ○ |  |  |  |  |
| Interview | | ○ |  | ○ | ○ | ○ |
| Physical measurements | Height | ○ |  |  |  |  |
|  | Weight | ○ |  | ○ | ○ | ○ |
| Scientific examinations | Systolic blood pressure | ○ |  | ○ | ○ | ○ |
|  | Diastolic blood pressure | ○ |  | ○ | ○ | ○ |
|  | Heart rate | ○ |  | ○ | ○ | ○ |
|  | Biochemical data |  |  | ○ |  | ○ |
|  | Fundoscopy | ○ |  |  |  |  |
|  | Vision test, refractometry | ○ |  |  |  |  |
|  | Functional visual acuityt |  |  | ○ | ○ | ○ |
|  | BUT | ○ |  | ○ | ○ | ○ |
|  | Keratoconjunctival disorder | ○ |  | ○ | ○ | ○ |
|  | Schirmer’s test | ○ |  | ○ | ○ | ○ |
| Subjective dry eye evaluation | DEQS | ○ |  | ○ | ○ | ○ |
| Consumption of trial product | |  |  | [figure not shown] | | |
| Journal records | |  |  | [figure not shown] | | |

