10.3. Survey and examination content

See the schedule above.

| Item | Content | |
| --- | --- | --- |
| Lifestyle questionnaire | Medical history, medical product and health food intake, allergies, smoking status, alcohol intake, subjective dry eye symptoms (DEQS), etc. | |
| Interview | Inquire about physical condition, check for adverse events | |
| Physical measurements | Height*^1^, weight, BMI | |
| Scientific examinations | Systolic blood pressure, diastolic blood pressure, heart rate, biochemical data(total protein, aspartate aminotransferase, alanine transaminase, lactate dehydrogenase, alkaline phosphatase, gamma-glutamyl transferase, urea nitrogen, creatine, uric acid, total cholesterol, low-density lipoprotein cholesterol, high-density lipoprotein cholesterol triglyceride, glucose, haemoglobin A1c) | |
|  | Fundoscopy | Examination by physician during interview*^1^ |
|  | Vision test | Measured using a visual examination device*^1^ |
|  | Functional vision test, | Examined using a functional optometer*^2^ |
|  | Refractometry | Examined using autorefractor keratometer*1 |
|  | BUT | Fluorescein BUT*^2^ |
|  | Keratoconjunctival disorder | Fluorescein stain test*^2^ |
|  | Schirmer’s test | *^3^ |

1. ^1^: Performed at preliminary examination only
2. ^2^: Performed starting with pre-consumption examination
3. ^3^: Performed at preliminary examination and eighth-week examination

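### Student's t-test for between-group biochemistry and for age is allowed only after a non-significant F-test, and no test is named when the F-test is significant

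*Protocol*

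**What the plan says.** Protocol 15.1 (3) sets the test for placebo versus royal jelly in the biochemical analysis: "the F-test, followed by Student’s t-test (p≥0.05 by the F-test) will be used for between-group comparisons". For the baseline table it states: "Student’s t-test (p ≥ 0.05 by the F-test) will be used for comparison of age". Both sentences make Student's test conditional on the F-test not reaching significance, and both stop there.

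Two other rules in the same part of the protocol might be thought to supply the missing branch. The opening efficacy paragraph has items "compared between the trial group and the placebo group using a 2-sample t-test". The safety paragraph (headed 16.2) says that "measurements before consumption and at each time point after consumption will be compared using a 1-sample t-test" and sets the level with "The significance level will be 2-sided 5"%.

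Section 6.1 plans "25 subjects taking the trial product and 25 subjects taking the placebo". Section 10.3 lists the analytes, beginning "total protein, aspartate aminotransferase, alanine transaminase, lactate dehydrogenase, alkaline phosphatase, gamma-glutamyl transferase". The examination schedule marks "Biochemical data" at the pre-consumption visit and at week 8.

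**The concern.** A rule that picks the test from a preliminary variance test needs two branches, and this one has only the first. When the F-test is significant, the protocol forbids Student's test by implication and puts nothing in its place. The analyst then has to choose among Welch, a rank test, a transformation or Student's test regardless, with the data already in view.

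The pre-test is also a poor design choice. The F-test for variances is sensitive to non-normality, and skewness is plausible for analytes such as triglyceride and gamma-glutamyl transferase. It can therefore be significant when the two arms have identical distributions. Where it is not significant, the Student's test that follows is conditioned on a look at the same data and need not keep its nominal 5%.

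At stake is whether the between-group biochemistry results, a listed safety item, come from a test fixed in advance.

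**Working it through.** The protocol gives no figure on this point to reproduce.

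**Does any other sentence fill the gap?** The general 2-sample t-test sentence is written for the efficacy items, does not say whether variances are pooled, and is not offered as a fallback. The safety paragraph's 1-sample test compares before with after, not arm with arm. Neither supplies the missing branch.

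**How often is the branch reached?** Inputs from the protocol: 15 analytes (10.3, counting HDL cholesterol and triglyceride separately), F-test threshold 0.05 (15.1), 25 per arm (6.1), biochemistry at two visits (schedule). With normal data and equal variances each F-test is significant with probability 0.05.

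- One time point: expected number without a test = 15 × 0.05 = 0.75. P(at least one) = 1 − 0.95^15 = 0.537.
- Both time points, if both are compared: expected 30 × 0.05 = 1.5. P(at least one) = 1 − 0.95^30 = 0.785. With age added, 1 − 0.95^31 = 0.796.

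The probabilities assume independence; the expected counts do not. Under any dependence, the single-time-point probability lies between 0.05 (all analytes moving together) and 15 × 0.05 = 0.75 (the union bound).

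Departures from the ideal case raise the per-comparison rate. The SD ratios and skewness are assumed, since the protocol gives none; all cases are 25 v 25.

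- Normal, SD ratio 1.5: the F-test is significant in 49% of comparisons. Check: the upper 2.5% point of F(24, 24) is 2.269, and 2.269 / 1.5² = 1.009, which F(24, 24) exceeds with probability 0.49.
- Normal, SD ratio 2: 91%.
- Identical log-normal arms: 12% at log-SD 0.3, about 23% at log-SD 0.5, 35% at log-SD 0.7.

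**What is the error rate when Student's test is used?** Simulation under the null, two-sided 5%, normal data, assumed SD ratio 1.5:

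| Arms (assumed) | More variable arm | Student, given F-test not significant | F-test, then Student or Welch, overall | Welch throughout |
|---|---|---|---|---|
| 25 v 25 | either | 5.7% | 4.9% | 4.9% |
| 25 v 20 | smaller | 6.9% | 5.4% | 5.0% |
| 25 v 20 | larger | 4.6% | 4.6% | 5.0% |
| 25 v 18 | smaller | 7.4% | 5.6% | 5.0% |
| 25 v 18 | larger | 4.3% | 4.5% | 5.0% |

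The third column applies only to data sets that pass the F-test, about half of them at 25 v 25. At SD ratio 2 and 25 v 25 the conditional figure is 7.8%, but only about 9% of data sets get that far. For identical log-normal arms (log-SD 0.5, 25 v 25) it is about 2.7%, below nominal.

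**What does Welch cost and deliver?** At a difference of 0.8 SD, equal variances and 25 per arm, simulated power is 0.7897 for Welch and 0.7903 for Student. Welch's error is 4.8% to 5.1% in the normal scenarios (25 v 25, 25 v 20 and 23 v 18, SD ratios 1 to 3). In the log-normal scenarios (log-SD 0.7, same arm sizes and ratios) it is 4.3% to 8.0%.

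**The case against.** The strongest reply is that the fallback after a failed variance check is ordinary SAP detail, and a SAP may exist. That would answer a protocol that was silent on the test. This protocol instead fixes a data-dependent rule and states half of it. A SAP could add the other half but would inherit the pre-test.

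The second reply is that little depends on it. This stands: biochemistry is neither a primary nor a secondary efficacy outcome, the safety paragraph relies on event tables and within-group tests, and a significance test on baseline age tells little in a randomized trial.

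A reader might infer three stronger things that the documents do not support.

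- *That the plan materially inflates type I error.* The 7.4% needs an assumed loss of 7 of 25 subjects from one arm, none from the other, and the larger SD in the depleted arm; with the larger SD in the other arm the figure is 4.3%. It is also a conditional rate. If Welch were the unstated fallback, the whole procedure would run at 4.5% to 5.6% in these scenarios.
- *That the exclusions in 14.1 will unbalance the arms for these tests.* Section 14.1 defines the efficacy set. The set for examination values in 14.2 (2) is completers, without the 80% intake or journal criteria. The biochemistry sentence sits under 15.1, so which set governs is arguable. Non-completion can still unbalance the arms, but the protocol gives no expected split.
- *That Welch makes every analyte's result valid.* It handles unequal variance. It does not cure skewness at about 25 per arm (up to 8.0% above) or multiplicity over 15 analytes.

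**Conclusion.** The point holds as a gap in a stated rule. For between-group biochemistry and for age, the protocol defines what to do when the F-test is not significant and leaves the alternative empty. Under the most favourable conditions, normal data with equal variances, the empty branch is reached at least once among 15 analytes at one time point with probability about 54%, assuming independence; related analytes would change that figure. Unequal variances or skewness make it more frequent. The harm is a test chosen after seeing the data.

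Distortion of the error rate where Student's test is used is a lesser matter: about 5.7% at 25 v 25 and 4.3% to 7.4% over the arm sizes examined, for normal data with an assumed SD ratio of 1.5. SD ratios, skewness and final arm sizes are all assumptions. Only safety and baseline comparisons are touched; the primary outcomes are not. This is a desirable correction, not a condition for the trial's conclusions.

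**What to change.** Delete the F-test step from both sentences in 15.1 (3). State that all between-group biochemistry comparisons use Welch's unequal-variance t-test, reported as the mean difference with its 95% CI, and that age uses the same test if it is tested at all.

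The cost is a small edit to two sentences, with a power loss of about 0.0006 in the equal-variance example above (0.7903 − 0.7897). Every item then has a pre-specified, approximately valid test. Markedly skewed analytes and the number of comparisons would still need separate handling.

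### The safety section tests examination values only before versus after, so weight, blood pressure and heart rate are never compared with placebo, and its method for biochemistry is incomplete

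*Protocol*

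**What the plan says.** The safety section (numbered 16.2, although it follows 15.1) lists the examination values to be checked: "body weight, systolic blood pressure, diastolic blood pressure, heart rate, and biochemical data". Under its own heading for evaluation methods it gives one inferential rule for them: "To evaluate changes in examination values, measurements before consumption and at each time point after consumption will be compared using a 1-sample t-test". The level is two-sided 5%. Adverse events and abnormal variations are to be counted in a table.

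Section 15.1(3), on efficacy methods, is fuller. It has a between-arm test of change: "The amount of change from before consumption to each time point after consumption will be compared between the trial group and the placebo group", by a 2-sample t-test. The outcomes listed just above it, in 15.1(1) and (2), are the dry eye measures and functional vision. The same subsection also covers biochemistry: "For the biochemical analysis, paired t-tests will be used for within-group comparisons", and an F-test followed by Student's t-test "will be used for between-group comparisons (placebo vs. RJ").

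The trial is randomized and placebo-controlled (section 5), with "25 subjects taking the trial product and 25 subjects taking the placebo" (section 6.1). The schedule table has weight, blood pressure and heart rate measured before consumption and at weeks 4 and 8, and biochemistry before consumption and at week 8. Section 14.2 limits the examination-value safety set to subjects who complete the schedule.

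**The concern.** A before/after test asks whether the mean moved in one arm. The safety question is whether it moved because of the product, and only the contrast with placebo answers that. Both arms may move together, for example with season over the eight weeks, and the stated test attributes none of that movement to its source. Testing each arm separately does not help, because a significant result in one arm and a non-significant one in the other is not a test of the difference.

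The error can go either way. A shared change can look like a product effect on blood pressure or weight. A shared change in the opposite direction can cancel a real product effect, so that the RJ arm looks unchanged. For safety, the second error is the worse one.

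The biochemistry description is a lesser matter. A reader who goes to the safety section for the safety method will not learn that a placebo comparison is planned.

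**Working it through.** **Which items have a placebo comparison**

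| Item | Before/after test | Between-arm test |
|---|---|---|
| Weight, systolic BP, diastolic BP, heart rate | 16.2(2) | none |
| Biochemistry (15 analytes, section 10.3) | 16.2(2) and 15.1(3) | 15.1(3) only |
| Dry eye measures, functional vision | 15.1(3) | 15.1(3) |

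The gap is 4 measurements × 2 visits = 8 comparisons. For biochemistry the within-group parts agree: a 1-sample t-test on differences is the paired t-test (a check on simulated data gave identical p-values, 0.2509). What 16.2 lacks is the between-arm part.

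**Inputs**
- n = 25 per arm (section 6.1). Because section 14.2 keeps completers only, n = 20 is also shown. That figure is an assumption, since no dropout rate is given.
- Two-sided 5% (section 16.2).
- Drift d shared by both arms, in SDs of the change. The documents give neither a drift nor an SD, so d = 0.2 to 0.8 is assumed.
- The protocol has no figure of its own to reproduce here.

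**False signals under shared drift, no product effect**

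The before/after statistic in the RJ arm follows a noncentral t with n − 1 degrees of freedom and noncentrality d√n. At n = 25 and d = 0.4 the noncentrality is 0.4 × 5 = 2.0, and the probability of significance is 0.484. With p that probability, RJ significant and placebo not has probability p(1 − p).

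| d | RJ test significant, n = 25 | RJ test significant, n = 20 | RJ significant and placebo not, n = 25 |
|---|---|---|---|
| 0.2 | 16.1% | 13.6% | 13.5% |
| 0.3 | 30.2% | 24.7% | 21.1% |
| 0.4 | 48.4% | 39.7% | 25.0% |
| 0.5 | 67.0% | 56.5% | 22.1% |
| 0.8 | 97.0% | 92.4% | 2.9% |

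In a between-arm test of change the shared drift cancels: the expected difference is d − d = 0, and the false-positive rate is the nominal 5%. A simulation of 20,000 trials at d = 0.5 and n = 25 gave 5.1%.

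**Masking**

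Take a product effect of +0.5 SD and a shared drift of −0.5 SD. The expected change in the RJ arm is 0.5 − 0.5 = 0, so its before/after test is significant 5% of the time. The between-arm difference is still 0.5 SD. The between-arm test has noncentrality 0.5 × √(25/2) = 1.77 on 48 degrees of freedom, giving 41% power at n = 25 (34% at n = 20).

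**The case against.** Several points on the other side have force.

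- **Sections 15.1 and 16.2 do not contradict each other on biochemistry.** A reader might infer a contradiction, because one names a placebo comparison and the other does not. But 16.2 does not exclude that comparison, the within-group tests are the same, and both sections can be carried out as written. The description is incomplete, and that is all.
- **Multiplicity is a separate matter.** A reader might count 8 + 15 = 23 before/after tests per arm and blame this analysis for the resulting chance of a false signal. That chance comes from doing 23 tests at 5%. It would be the same for 23 between-arm tests, and 15 of the 23 concern analytes that already have a placebo comparison.
- **Not every usual cause of drift applies.** Regression to the mean would need selection on the measured values, and the criteria in 7.1 and 7.2 do not select on weight, blood pressure, heart rate or biochemistry results. Habituation to the clinic is partly absorbed, since blood pressure and heart rate are already taken at the preliminary visit. Season remains plausible.
- **No safety decision hangs on the p-value.** Under section 12.2 the principal investigator judges abnormal changes against reference values and published criteria. It would go too far to say that safety is decided by this test.
- **The before/after test has more power when there is no drift.** For a 0.5 SD change at n = 25 it has 67% against 41% between arms, and over-flagging is the cautious direction.

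These points narrow the finding without removing it. The extra power is power to detect any change, whatever its cause, and the cautious direction holds only when drift adds to the product effect. It also cannot be said that the matter was left to the statistical analysis plan, because the protocol itself names the test.

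**Conclusion.** The point stands in limited form. Weight, systolic and diastolic blood pressure and heart rate have no placebo comparison anywhere in the protocol, and 16.2 gives an incomplete account of the biochemistry method. The stated test cannot distinguish a product effect from a change common to both arms.

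How much this matters depends on a drift that the documents do not give, so the percentages under the working illustrate a range and predict nothing for this trial. They also assume normally distributed changes with equal SD in the arms. With no drift at all, the before/after false-positive rate is the nominal 5%.

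Two readings of the wording should be kept modest. Section 16.2 does not say that its test is done in each group; that is the natural reading from the parallel sentence in 15.1(3), and a test pooling both arms would be less informative still. Nor is the placebo arm left unanalysed: it may get its own before/after test, and its events are tabulated. What is missing is the contrast between arms. The change is worth making because the remedy is almost free.

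**What to change.** In 16.2(2), state the between-arm analysis. For example: *For body weight, systolic and diastolic blood pressure, heart rate and each biochemistry item, the change from pre-consumption to each later measurement will be compared between the RJ and placebo groups by a 2-sample t-test and reported as a difference in mean change with its 95% confidence interval. Conclusions about a product effect will rest on this comparison. Changes within each group will be shown descriptively.*

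This is the test of change that 15.1(3) already uses for efficacy. Adjustment for the pre-consumption value is an option, not a requirement. The interval matters more than the p-value, because power at this size is modest: at 25 per arm, 41%, 79% and 93% for true differences of 0.5, 0.8 and 1.0 SD of the change (34%, 69% and 87% at 20 per arm). A non-significant difference should not be read as evidence of no effect.

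Move the biochemistry method from 15.1(3) to 16.2, or cross-refer, so that both sections state the same analysis and say that it is applied to change.

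The cost is a wording amendment and its ethics committee approval under section 16.3. The measurements are already planned in both arms.
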